## Abstract

Fetal growth restriction (FGR) is one of the leading causes of perinatal morbidity and mortality. Many studies have reported an association between FGR and fetal Doppler indices focusing on umbilical artery (UA), middle cerebral artery (MCA), and ductus venosus (DV). The uteroplacental-fetal circulation which affects the fetal growth consists of not only UA, MCA, and DV, but also umbilical vein (UV), placenta and uterus itself. Nevertheless, there is a paucity of large-scale cohort studies that have assessed the association between UV, uterine wall, and placental thickness with perinatal outcomes in FGR, in conjunction with all components of the uteroplacental-fetal circulation. Therefore, this multicenter study will evaluate the association among UV absolute flow, placental thickness, and uterine wall thickness and adverse perinatal outcome in FGR fetuses. This multicenter retrospective cohort study will include singleton pregnant women who undergo at least one routine fetal ultrasound scan during routine antepartum care. Pregnant women with fetuses having structural or chromosomal abnormalities will be excluded. The U-AID indices (UtA, UA, MCA, and UV flow, placental and uterine wall thickness, and estimated fetal body weight) will be measured during each trimester of pregnancy. The study population will be divided into two groups: (1) FGR group (pregnant women with FGR fetuses) and (2) control group (those with normal growth fetus). We will assess the association between U-AID indices and adverse perinatal outcomes in the FGR group and the difference in U-AID indices between the two groups.

## Introduction

Fetal growth restriction (FGR), which is found in approximately 3–8% of pregnancies, is a leading cause of perinatal morbidity and mortality [1, 2]. The definition of FGR differs according to clinical guidelines and author groups [3–5]. The International Society of Ultrasound in Obstetrics and Gynecology (ISUOG) defines FGR as a pathologic condition in which the fetus cannot reach its own determined genetic growth. According to the (ISUOG) practice guidelines, the finding of an abnormal uterine artery (UtA) or umbilical artery (UA) on Doppler examination should be accompanied by an abdominal circumference (AC) or estimated fetal weight (EFW) of less than the 10^th^ percentile for gestational age to diagnose early FGR unless the AC or EFW is less than the 3^rd^ percentile [5]. In contrast, the American College of Obstetricians and Gynecologists (ACOG) and the Society for Maternal-Fetal Medicine (SMFM) define FGR as a fetus whose AC or EFW is less than the 10^th^ percentile [2, 3].

Even though the definition of FGR may defer between guidelines, consistently worse perinatal outcomes of FGR fetuses with abnormal UA Doppler results have been reported compared to those with normal UA Doppler results [6–9]. Therefore, fetal vascular Doppler examinations, including UA Doppler, are important in distinguishing a pathologically growth-restricted fetus from a small but healthy fetus. Several studies predicted the perinatal outcomes of fetuses with growth restriction and these studies mainly focused on the Doppler examination of specific vessels, such as the UA, MCA, or ductus venosus (DV) [6–12]. However, besides the UA, MCA, or DV, uteroplacental-fetal circulation also consists of other components affecting fetal growth. For example, umbilical vein (UV) flow and placental thickness, which are components of uteroplacental-fetal circulation, have already been shown to be associated with fetal growth. Ferrazzi et al. reported that UV flow per unit head circumference (HC) was decreased in FGR fetuses [13]. Another study reported that venous flow was also reduced in FGR fetuses [14]. In a previous study assessing the correlation between placental thickness and small for gestational age (SGA) neonates, the placental thickness-to-EFW ratio was higher in SGA neonates compared to non-SGA neonates [15]. In addition, a thick placenta was reported to be associated with adverse perinatal outcomes [16]. In this research, we aim to focus on the uterine wall, in conjunction with the umbilical vein. The uterine wall is a distinctive aspect of this study, as it has been neglected in previous research on FGR. The causes of a thick uterine wall observed in ultrasonography are typically categorized into three main factors: sustained uterine wall contractions, adenomyosis, and uterine fibroids [17, 18]. If a thick uterine wall is observed in a pregnant woman without a history of uterine fibroids or adenomyosis, it may be attributed to a sustained uterine contraction. The uterine contractions are known to lead to a decrease in uteroplacental blood flow [18–20]. Taking this into consideration, uterine wall thickness may be associated with the uteroplacental blood flow. The hypothesis that uterine wall thickness may impact fetal growth is one of the key starting points for our research.

Therefore, we aim to evaluate the association of UV absolute flow, placental thickness, and uterine wall thickness with adverse perinatal outcomes in the FGR fetuses, ultimately seeking to validate their involvement in the pathophysiology of FGR. In addition, we will comprehensively assess various uteroplacental-fetal biometrics and Doppler indices according to fetal growth in each trimester of pregnancy to establish a prediction model for adverse perinatal outcomes in FGR fetuses using these ultrasonographic measurements.

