### Exclusion criteria

Pregnant women with missing value of UV flow, placental thickness, and uterine wall thicknessPregnant women with fetuses with possible structural anomalies or abnormal insertion of umbilical cord found on ultrasoundPregnant women with fetuses with chromosomal abnormalitiesPregnant women who are proven to have an intrauterine infectionPregnant women who have limited data on clinical characteristics related to pregnancy and perinatal outcome

In this study, we define FGR as a status where both of the following 2 conditions are met; (1) an EFW or AC below the 10th percentile for gestational age during the second or third trimester of pregnancy and (2) birthweight below the 10th percentile for gestational age [3]. The INTERGROWTH-21^st^ growth chart is used for biometry and birthweights [21]. The FGR group includes both early-onset FGR and late-onset FGR. The control group includes participants with a fetus whose EFW and AC are in the range of 10^th^ to 90^th^ percentile for gestational age. The control group will be selected through 1:1 matching based on age, parity, and presence or absence of preeclampsia. The clinical information and U-AID indices of pregnant women who delivered between March 2016 and March 2023 will be extracted from the medical records.

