### Outcomes

The primary outcome is the association of UV absolute flow, placental thickness, and uterine wall thickness with adverse perinatal outcomes in the FGR group to differentiate genuinely growth-restricted fetuses from those who are constitutionally small. The secondary outcome is to evaluate the differences in U-AID indices (UtA, UA, MCA, and UV flow, placental and uterine wall thickness, and estimated fetal body weight) between the FGR and control group will be evaluated.

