### Statistical methods

The distribution of U-AID indices according to AC, BPD, EFW and gestational age will be assessed. The study population will be divided into two groups, the FGR group which includes participants with FGR fetuses, and the control group includes participants with normal growth fetus. First of all, we will compare the differences in U-AID indices according to adverse perinatal outcomes with in FGR group. Secondly, the difference of U-AID indices between the two groups will be compared. Continuous variables will be presented as the mean ± standard deviation or median [interquartile range] and compared by the Mann-Whitney U test or independent t-test according to the distribution of each variable. Categorical variables will be presented as the number of observations (percent) and compared by the chi-squared test or Fisher’s exact test. To determine the contribution of all the collected variables and Doppler findings to adverse perinatal outcomes of the FGR fetuses, multivariable logistic regression analysis with backward stepwise elimination will be used.

All statistical analyses will be performed using IBM SPSS statistics version 23.0 (SPSS Inc., Chicago, IL, USA) and R version 4.2.1 (http://www.r-project.org).

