## Discussion

The novelty of this study lies in its comprehensive examination of all the parts within the pathway of blood flow from mother to fetus. The rationale behind this study design stems from the objective to investigate the pathophysiology of fetal growth within the clinically observable range of ultrasonography, encompassing the processes that involve UtA, uterine wall, placenta, UV and fetal growth, The aim is to elucidate the pathophysiology of fetal growth. Through this study, we aim to find the association between new ultrasonographic indices, including UV absolute flow, and placental and uterine wall thickness and perinatal outcome of growth restricted fetuses. As it is significant to distinguish growth restricted fetuses with adverse perinatal outcomes from the constitutionally small fetuses, we posit that this study may contribute to the identification of new risk factors or the development of a prediction model for genuinely growth restricted fetuses in future study. By evaluating and comparing the various ultrasonographic uteroplacental-fetal biometric measurements and Doppler indices according to fetal growth, we can determine how much each ultrasonographic index influences fetal growth. Through this finding, we can provide evidence for future studies on the pathophysiology of FGR fetuses. Lastly, we can also assess the distribution of umbilical vein flow values according to estimated fetal weight in each trimester of pregnancy.

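### An association found only among FGR fetuses is prognostic; by itself it can neither confirm nor refute a role of the three indices in causing FGR

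*Protocol article*

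**What the plan says.** All references are to the protocol article.

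- **Hypothesis (Introduction).** The indices are thought to act on growth. Wall thickness is linked to uteroplacental blood flow, and "The hypothesis that uterine wall thickness may impact fetal growth is one of the key starting points for our research".
- **Claim (Introduction, aims).** The association of the three indices with adverse outcome in FGR fetuses is to be evaluated, "ultimately seeking to validate their involvement in the pathophysiology of FGR".
- **Primary analysis (Outcomes; Statistical methods).** "The primary outcome is the association of UV absolute flow, placental thickness, and uterine wall thickness with adverse perinatal outcomes in the FGR group". Its stated purpose there is "to differentiate genuinely growth-restricted fetuses from those who are constitutionally small". The first planned comparison is in the same group: "we will compare the differences in U-AID indices according to adverse perinatal outcomes with in FGR group".
- **Selection of that group (text under Exclusion criteria).** Two conditions must both hold: "an EFW or AC below the 10th percentile for gestational age during the second or third trimester of pregnancy", and a birthweight under the 10th percentile.
- **FGR versus control (Outcomes; Statistical methods).** This comparison of the U-AID indices is secondary. Controls are matched 1:1 on age, parity and preeclampsia.
- **Discussion.** Of comparing the indices according to fetal growth, it says "we can determine how much each ultrasonographic index influences fetal growth", and then that this finding can provide evidence for future work on FGR pathophysiology.

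**The concern.** The claim in the aims concerns how FGR arises. The analysis it is attached to starts after FGR has arisen. By admitting only fetuses that are already small, before and at birth, the primary analysis restricts the very step through which the indices are supposed to work. It answers which growth-restricted fetuses do badly, not whether an index helps to make a fetus growth-restricted.

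Followed as written, a prognostic association would be reported as validating a role in FGR. The error can run both ways. An index that worsens outcome without touching growth would give a positive result inside FGR. An index that does cause FGR could give a weak, absent or reversed one.

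**Working it through.** **1. The plan's own figure.** Sample size gives a minimum of 472 FGR women but no effect size, SD or event rate, so 472 cannot be reproduced. The inflation can: 472 × 1.10 = 519.2 (stated 519), and 472 / 0.90 = 524.4, rounded up to 525 per group (stated 525, total 1,050).

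**2. What 472 can detect inside FGR.** Assume two-sided 5%, read the stated β-error of 80% as 80% power, and let p be the assumed adverse-outcome rate in FGR. Then d = (1.960 + 0.842) × √[1/(472p) + 1/(472(1−p))]. For p = 10%, 20%, 30% and 50%, d = 0.43, 0.32, 0.28 and 0.26 SD.

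**3. Simulation of an index that truly causes FGR.** All effect sizes are assumptions; the documents give none. There are 2,000,000 pregnancies, with index X standard normal (higher = worse), FGR the lowest 10% of a size score G, and the intercept set for a 5% overall adverse-outcome rate. r takes the values 0.2, 0.3 and 0.5.

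- A: G = −rX + noise (variance 1); logit(outcome) = a + 1.8 × FGR. Outcome depends only on being FGR.
- B: G as in A; logit(outcome) = a − 0.8 × G. Outcome depends on size continuously.
- C: X causes a pathology with 6% prevalence and log-odds slope r/0.3; pathology lowers size by 1.8 SD; logit(outcome) = a + 2.0 × pathology. FGR is then a mixture, 37% pathological.
- D: as A, with an unmeasured U that lowers size (−0.5U) and raises risk (+0.8U).

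Results for r = 0.2 / 0.3 / 0.5:

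| Scenario | OR per SD, population | OR per SD, inside FGR | Index difference by outcome inside FGR (SD) | FGR minus non-FGR (SD) |
|---|---|---|---|---|
| A | 1.12 / 1.18 / 1.32 | 1.00 / 1.00 / 1.00 | 0.00 / 0.00 / 0.00 | 0.38 / 0.58 / 0.98 |
| B | 1.17 / 1.27 / 1.47 | 1.03 / 1.06 / 1.11 | 0.03 / 0.05 / 0.08 | 0.38 / 0.58 / 0.98 |
| C | 1.16 / 1.23 / 1.35 | 1.33 / 1.44 / 1.66 | 0.30 / 0.41 / 0.62 | 0.22 / 0.33 / 0.48 |
| D | 1.14 / 1.20 / 1.36 | 0.94 / 0.90 / 0.83 | −0.06 / −0.09 / −0.15 | 0.39 / 0.58 / 0.97 |

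**4. Reading the table.**

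- A: the association vanishes.
- B: it is attenuated. On the log scale ln 1.03 / ln 1.17 = 0.19 and ln 1.11 / ln 1.47 = 0.27, so about a fifth to a quarter remains. The difference by outcome (at most 0.08 SD) lies well below anything in step 2.
- C: it is inflated. ln 1.33 / ln 1.16 = 1.9 and ln 1.66 / ln 1.35 = 1.7. The outcome rate in FGR was 11%, so the relevant entry in step 2 is about 0.4 SD: 0.30 falls short, 0.41 is borderline, 0.62 is detectable.
- D: the sign is reversed.

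The cause is real in all four scenarios. Only the last column points the right way throughout. It compares FGR with everyone else, not with the plan's matched controls.

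**The case against.** The strongest reply is that the plan does not treat FGR as one homogeneous growth failure. The Introduction and Outcomes describe the small fetuses as a mixture of pathological and healthy, and give the primary analysis the task of telling them apart. In that setting (scenario C) a cause of the pathology shows up inside FGR more strongly than in the population. The Introduction also reports consistently worse outcomes in FGR with abnormal than with normal umbilical artery Doppler, which is itself a flow-outcome association inside FGR. The Discussion links pathophysiology to comparison by fetal growth and words its hopes cautiously. On this view the defect is one over-strong phrase.

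Most of that stands, and it rules out three stronger readings.

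- A reader might infer that a true cause of FGR must look almost null in the primary analysis. That holds only if outcome depends on size alone, which is not the documents' premise. Selection restricts growth but does not hold it fixed: severity varies, EFW or AC suffices for the prenatal condition, and early- and late-onset cases are both included.
- A reader might infer that no within-FGR result bears on pathophysiology at all. Scenario C shows otherwise. Such a result can be supporting evidence; it cannot decide the matter alone.
- A reader might infer that the plan never connects the FGR-control comparison to pathophysiology. The Discussion partly does.

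What the reply does not remove is the aim itself, which hangs the word validate on the within-FGR association. To read that association as the mixture case, one must already assume that the index drives the pathology.

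**Conclusion.** The point holds as a mismatch between the stated aim and the comparison it is attached to. For a true cause of FGR, the within-FGR odds ratio per SD ranged from 0.83 to 1.66 across four plausible structures, while the population value stayed between 1.12 and 1.47. The data planned for the primary analysis cannot show which structure applies, so neither a positive nor a null primary result is enough on its own to settle a causal role.

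The figures rest on assumed effect sizes, a single 10% size cut-off in place of the plan's two-part definition, and a 5% overall outcome rate. The qualitative conclusion needs only the selection rule and the hypothesis as the article states them. The prognostic purpose given under Outcomes is legitimate and unaffected.

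**What to change.** 1. In the Introduction (aims) and Outcomes, limit the primary conclusion to prognosis within FGR, including the separation of genuine FGR from constitutionally small fetuses. Remove the statement that this association will validate involvement in FGR pathophysiology.
2. Name the planned FGR-control comparison of the three indices as the analysis for the pathophysiology aim, in line with the Discussion's sentence on comparison by fetal growth. Preferably use measurements that precede the FGR diagnosis. Table 1 offers wall thickness from the first trimester, and placental thickness and UV flow from the second.
3. State the limits of that comparison. It is also observational. Matching on preeclampsia may remove part of the placental pathway. UV absolute flow in ml/min depends on fetal size, so lower flow in FGR may partly reflect a smaller fetus. The Discussion itself expects missing Doppler values in fetuses of normal weight.

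Cost: rewording, with no new data collection and no change to the primary model. Restricting to measurements before diagnosis may leave fewer women, mainly among early-onset cases. The downside is a narrower primary claim.

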## Methods

### Study design and population

The U-AID study is a multicenter retrospective cohort study which is led by an obstetric ultrasonography research society of Korean Society of Ultrasound in Obstetrics and Gynecology (KSUOG). This is conducted in 13 academic hospitals in the Republic of Korea. This study includes singleton pregnant women who undergo fetal ultrasound during routine antepartum surveillance. The eligible participants are pregnant women over 19 years old who can understand information about the current study and make decisions on whether to voluntarily participate in the study. There is no limitation on gestational age but pregnant women with fetuses found to have structural anomalies, abnormal insertion of umbilical cord, chromosomal abnormalities, or any kind of congenital infection will be excluded. The abnormal insertion of umbilical cord includes velamentous insertion and marginal insertion of umbilical cord. Of note, pregnant women with missing value of UV flow, placental thickness, and uterine wall thickness will be excluded.

### Inclusion criteria

Singleton pregnant womenAge older than 19 yearsParticipants who have no difficulty understanding information on the current study so they can voluntarily decide to participate and provide fully informed consentReceiving fetal ultrasound for routine antepartum surveillance

### Exclusion criteria

Pregnant women with missing value of UV flow, placental thickness, and uterine wall thicknessPregnant women with fetuses with possible structural anomalies or abnormal insertion of umbilical cord found on ultrasoundPregnant women with fetuses with chromosomal abnormalitiesPregnant women who are proven to have an intrauterine infectionPregnant women who have limited data on clinical characteristics related to pregnancy and perinatal outcome

In this study, we define FGR as a status where both of the following 2 conditions are met; (1) an EFW or AC below the 10th percentile for gestational age during the second or third trimester of pregnancy and (2) birthweight below the 10th percentile for gestational age [3]. The INTERGROWTH-21^st^ growth chart is used for biometry and birthweights [21]. The FGR group includes both early-onset FGR and late-onset FGR. The control group includes participants with a fetus whose EFW and AC are in the range of 10^th^ to 90^th^ percentile for gestational age. The control group will be selected through 1:1 matching based on age, parity, and presence or absence of preeclampsia. The clinical information and U-AID indices of pregnant women who delivered between March 2016 and March 2023 will be extracted from the medical records.

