### Adverse perinatal outcomes

Pregnancy and perinatal outcomes will be acquired from medical charts. The adverse perinatal outcomes of the current study are listed in Table 2. The composite morbidity of neonates is defined as one of the following: sepsis, respiratory distress syndrome, necrotizing enterocolitis, or intraventricular hemorrhage before discharge.

**Table 2 pone.0298060.t002:** Adverse perinatal outcomes in the U-AID cohort.

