**Pregnancy outcomes**
Preeclampsia
Emergency cesarean section due to non-reassuring fetal heartbeat
Intrauterine fetal demise

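### The secondary FGR-control comparison uses 1:1 matched controls but only independent-samples tests, and preeclampsia is, unexplained, both a matching factor and a listed adverse outcome

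*Protocol article*

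**What the plan says.** The group definitions, at the end of the Exclusion criteria section, fix how controls are found: "The control group will be selected through 1:1 matching based on age, parity, and presence or absence of preeclampsia".

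The Adverse perinatal outcomes section says "The adverse perinatal outcomes of the current study are listed in Table 2", and the first entry under pregnancy outcomes in that table is "Preeclampsia".

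The controls are used in one comparison, the secondary outcome: "Secondly, the difference of U-AID indices between the two groups will be compared". For continuous variables, Statistical methods says they are "compared by the Mann-Whitney U test or independent t-test according to the distribution of each variable"; categorical variables are "compared by the chi-squared test or Fisher’s exact test". No paired or conditional method, and no method that adjusts for the matching factors, is named for this comparison. The only regression named is a logistic model for adverse outcomes of the FGR fetuses, which does not involve the controls.

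The primary outcome is the "association of UV absolute flow, placental thickness, and uterine wall thickness with adverse perinatal outcomes in the FGR group". It uses no controls.

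**The concern.** There are two separate issues, both confined to the secondary comparison.

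**Pairs analysed as independent.** One-to-one matching produces pairs. If the matching factors are related to an index, the two values in a pair are positively correlated, and the variance of the FGR-control difference is smaller than an independent-samples test assumes. The stated tests then report standard errors that are too large and give away precision that the matching was meant to buy. This is a mismatch between the stated design and the stated tests, so it is not a detail left to a fuller analysis plan.

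**Two roles for preeclampsia.** The plan treats preeclampsia as a factor to be equalised when controls are chosen and, elsewhere, as an adverse outcome of the pregnancy. It gives no reason. Matching forces the same frequency in both groups. Any part of an index difference that runs through preeclampsia is therefore removed, and the controls have the preeclampsia frequency of the FGR group rather than that of normally growing pregnancies. Without a stated target, a reader cannot tell whether a small FGR-control difference means that the index differs little or that part of the difference was matched away.

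**Working it through.** **The plan's own figures.** The Sample size section gives a base of 472 FGR participants, a 10% loss rate, and a total of 1,050 (525 + 525). Check: 472 / (1 − 0.10) = 524.4, rounded up to 525; 2 × 525 = 1,050. The total reproduces. (The 519 in the same section is 472 × 1.1 = 519.2; that is a separate matter.) The base of 472 cannot be reproduced, because no effect size, SD or event rate is given.

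**Ignoring the pairs.** Inputs: two-sided α = 0.05 (sidedness is assumed; the protocol gives only 0.05); the stated 80% read as power; 472 pairs; equal variances; within-pair correlation ρ, which is **assumed** at 0.05 to 0.3 because the documents give none. The effect is set to what an unpaired test detects with 80% power if ρ = 0: d = (1.96 + 0.84) × √(2/472) = 0.182 SD.

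- Overstatement of the standard error: 1/√(1−ρ) − 1
- True type I error of the unpaired test: 2 × [1 − Φ(1.96/√(1−ρ))]
- True power of the unpaired test: Φ((2.80 − 1.96)/√(1−ρ))
- Power of the paired test: Φ(2.80/√(1−ρ) − 1.96)

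| ρ | SE too large by | Type I error | Power, unpaired | Power, paired | Points lost |
|---|---|---|---|---|---|
| 0 | 0% | 5.0% | 80.0% | 80.0% | 0 |
| 0.05 | 2.6% | 4.4% | 80.6% | 82.0% | 1.4 |
| 0.1 | 5.4% | 3.9% | 81.3% | 84.0% | 2.7 |
| 0.2 | 11.8% | 2.8% | 82.7% | 87.9% | 5.2 |
| 0.3 | 19.5% | 1.9% | 84.3% | 91.8% | 7.5 |

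**Matching on preeclampsia.** The documents give neither the frequency of preeclampsia nor its effect on any index. **Assumed:** 10-30% in the FGR group, 3-5% in controls not matched on it, and an index shift of 0.3 to 1 SD in the same direction as the FGR effect.

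- Preeclamptic women among 525 controls: matched, 525 × 0.10 = 53 to 525 × 0.30 = 158; not matched on it, 525 × 0.03 = 16 to 525 × 0.05 = 26.
- Part of the difference removed = (frequency in FGR − frequency in unmatched controls) × shift:

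| FGR vs unmatched controls | Shift 0.3 SD | Shift 1 SD |
|---|---|---|
| 10% vs 5% | 0.015 SD | 0.05 SD |
| 10% vs 3% | 0.021 SD | 0.07 SD |
| 30% vs 5% | 0.075 SD | 0.25 SD |
| 30% vs 3% | 0.081 SD | 0.27 SD |

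The range is 0.015 to 0.27 SD. For scale, the detectable difference above is 0.182 SD, so the removed part runs from negligible to larger than that difference.

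**The case against.** **The two roles sit in different analyses.** A reader might infer that the plan matches on its own outcome and that the main result is therefore compromised. The documents do not support this. Table 2 outcomes serve the primary question, which is answered within the FGR group. In the matched comparison the dependent variables are the U-AID indices, not preeclampsia. This objection stands and limits the point to the secondary outcome.

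**Equal preeclampsia status may be a legitimate target.** A reader might also infer that the comparison is simply biased toward no difference. That is true only if the total FGR-control difference is wanted, and the protocol does not say so. The Discussion describes the pathway under study as "encompassing the processes that involve UtA, uterine wall, placenta, UV and fetal growth", without mentioning preeclampsia, so it cannot be cited to show that preeclampsia lies on that pathway or that particular indices suffer most. What remains is that the choice is unexplained and sits awkwardly with Table 2.

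**The unpaired tests err on the safe side.** They do, and at a correlation near zero the loss is trivial. The power figures are also illustrative: the Sample size section ties its calculation to a minimum number of FGR participants and not expressly to this comparison. The cost is precision, not false positives.

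**The sentence on tests is general.** It also covers the comparison within the FGR group by adverse outcome, where independent-samples tests are right. That is so, but the section names nothing else for the matched comparison.

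**Conclusion.** The point holds for the secondary FGR-control comparison only.

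The stated tests do not fit the stated 1:1 matching. At an assumed within-pair correlation of 0.05 to 0.3, the standard errors are about 3% to 20% too large, the actual type I error is about 4.4% to 1.9%, and about 1 to 8 points of power are lost. The direction is conservative.

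The dual role of preeclampsia needs an explanation. As written, the comparison estimates the difference at equal preeclampsia frequency. The part removed is 0.015 to 0.27 SD on assumed frequencies and an assumed index shift, none of which come from the documents. Whether that counts as bias depends on a target that the protocol has not stated. The primary analysis is untouched.

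**What to change.** 1. For the FGR-control comparison only, replace the unpaired tests with paired or matching-adjusted ones: paired t-test or Wilcoxon signed-rank for continuous indices; McNemar or conditional logistic regression for binary ones; or a mixed model with pair as a random effect. The mixed model can keep a woman whose partner lacks the index, which is useful because the Discussion expects some missing Doppler values in fetuses with normal estimated weight. Keep independent-samples tests for the comparison within the FGR group.

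2. On preeclampsia, choose one and write it down:
   - drop it from the matching factors; or
   - keep it, state that the target is the preeclampsia-independent difference, reconcile this with its place in Table 2, and add a sensitivity analysis using controls selected without matching on preeclampsia, or restricted to non-preeclamptic pregnancies.

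**Cost.** Slightly more analysis work. A restricted analysis is also smaller: on the assumed 10-30%, it would leave out about 53 to 158 of the 525 pairs. Further matching factors, such as centre or gestational age at scan, do not follow from these defects and are not part of this fix. They could cost pairs, since women may have up to three scan windows and Doppler data in controls may be scarce.
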